**Methods:**

Our aims are to: (1) deliver a coalition-based leadership intervention in eight U.S. health systems and their surrounding communities; (2) evaluate the impact of the intervention on organizational culture using a longitudinal, convergent mixed methods approach, and (3) evaluate the impact of the intervention on reduction of racial inequities in three clinical outcomes: a) early identification (time to antibiotic), b) clinical management (in-hospital sepsis mortality) and c) standards-based follow up (same-hospital, all-cause sepsis readmissions) using interrupted time series analysis.

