### Evaluation of impact on racial inequities in sepsis care (Aim 3)

We will evaluate the impact of the intervention on racial inequities in three sepsis-related outcomes: a) early identification (time to antibiotic), b) in-hospital mortality, and c) 30-day hospital readmission, using comparative interrupted times series (ITS) analysis. *Time to Antibiotics*: We will use hospital EHR data to determine the difference in mean time from hospital arrival to first antibiotic administration for all AA/B patients and NHW patients and between LatinX and NHW patients respectively presenting with sepsis. This value will be calculated quarterly. We will use *t-tests* to measure statistically significant differences between AA/B and NHW patients, and LatinX and NHW patients. A clinically meaningful difference in mean time to antibiotic would be 30 min [88–93]. *In-Hospital Mortality:* We will use hospital EHR data to determine the difference in quarterly in-hospital mortality rate by 30 days for AA/B and NHW patients and LatinX and NHW patients admitted for sepsis. Rates will be standardized by age and sex [94]. At each time point, we will use *t-tests* to measure statistically significant differences between AA/B and NHW patients, and LatinX and NHW patients. Currently, the rates of in-hospital mortality for AA/B are nearly double those of NHWs, and although the overall rates of sepsis mortality have remained relatively stable over the past decade, this gap has persisted [38]. A clinically meaningful difference in rates of in-hospital mortality would be greater than 1%. *30-Day Hospital Readmission:* We will use hospital EHR data to determine the difference in quarterly 30-day, same-hospital, all-cause readmission rate for AA/B patients and NHW patients, and LatinX and NHW patients with an index hospitalization for sepsis. Rates will be standardized by age and sex. We will use *t-tests* to measure statistically significant difference between AA/B and NHW patients, and LatinX and NHW patients. A clinically meaningful difference in rates of 30-day readmission would be 5% [7]. *Sepsis Case Identification:* We will identify hospital admissions for sepsis using validated International Classification of Diseases, Ninth Revision, Clinical Modification (ICD-9-CM) diagnosis procedure codes for infection and organ failure. This strategy [4], known as the Dombrovskiy strategy, is more sensitive than methods that use only ICD-9-CM codes for sepsis [95] and will allow the investigative team to include patients with sepsis that may have otherwise been missed by chart review that would still be eligible for evidence-based practices. For each health system, we expect to be able to observe at least 140 AA/B patients with sepsis each year (within a sample of MCCN member health systems, average inpatient volumes are over 19,000, patient population is approximately 12% AA/B, and nationally, sepsis is present in 6% of adult hospitalizations) [4]; therefore, we anticipate being able to track enough cases within each health system for each clinical outcome at each quarter.

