
#### Analytic approach

We will conduct a comparative interrupted times series (ITS) analysis to examine the relation between the intervention and racial/ethnic differences in sepsis clinical outcomes between AA/B and NHW patients and between LatinX and NHWs. The analysis will be performed separately for our three key outcomes: 1) time to antibiotics, 2) in-hospital mortality, and 30-day readmission and stratified by response to the intervention (change/no change) (Additional File 1; Supplemental Fig. 5). We will consider a pre-exposure to the intervention time beginning 2.5 years (10 quarters) prior to starting the intervention and a postexposure period comprising 2.5 years (10 quarters) following the start of the intervention, with estimates made at every calendar quarter. ITS will be utilized to determine the difference in quarterly rates over time between changers (systems that responded to the intervention) and non-changers, health systems that did not respond to the intervention. Subsequently, ITS allows us to detect if an intervention has impact above and beyond secular trends when randomization is not a feasible option, and is ideal for evaluation of data collected across multiple equally spread time points by testing the changes in the slope of an outcome over time [96]. Additionally, ITS requires at least eight observations pre and post intervention [97]. We will utilize generalized mixed effect models in conjunction with segmented regression to evaluate the effectiveness of our intervention [98]. The model will control for patient-level characteristics, including age, sex, insurance status, Charlson Comorbidity index, and admission through the Emergency Department or transfer from another acute care facility, and hospital-level characteristics including size, academic vs community hospital, number of intensive care beds, annual sepsis case volume. We will also account for seasonality based on calendar quarter by including a “season” term alone and interacted with the treatment indicator and will assess for any residual autocorrelation using autoregressive integrated moving average (ARIMA). To allow a marginal interpretation of results, we will use a linear probability model for all analyses. Because outcomes of patients within a hospital are expected to be correlated, we will account for these non-standard variance–covariance structures by clustering at the hospital level. All coefficients will be modeled as fixed effects.

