## Discussion

To our knowledge this is the first study to evaluate the impact of cultural change on racial inequities in care for patients with sepsis. Aligned with NIH and NIGMS priorities, the results of this study are expected to: 1) further the nascent scientific literature on conceptualizing and measuring structural racism and health outcomes, 2) generate community-driven innovations in sepsis care for dissemination through national organizations such as American College of Chest Physicians, and 3) provide much-needed evidence to inform local and national dialogue around structural racism and health. We fully recognize this study is an audacious proposition. It not only addresses a highly sensitive topic (structural racism), but it also seeks to make measurable change in the structural root causes of inequities in sepsis care. Importantly, we have balanced our ambitions for whole system change with careful operationalization of core constructs and detailed measurement approaches to understand the mechanisms of change. Further, the proposed study may be especially audacious in the context of COVID-19, which will likely strain organizational capacity to participate in change initiatives and is expected to change patient care processes and outcomes. As described above, a period of systematic stakeholder engagement will allow us to adapt the intervention for feasibility in the ever-changing context of COVID-19. Further, given the well-document impact of the pandemic in exposing structural racism and exacerbating racial inequities, the proposed study is both timely and urgent.

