We have anticipated several potential limitations in the proposed methodology. First, to mitigate social desirability bias (participants reporting socially acceptable, rather than authentic, responses) [99], we will use established techniques including attention to our own positionality and engagement of a diverse research team, engagement of a wide range of key informants across the project, use of interview guides with scripted probes to elicit details that would be difficult to misrepresent, encouraging participants to share both positive and negative experiences, and cultivating longitudinal relationships to encourage candor [100–102]. Second, clinical outcomes data will be derived from the EHR, which is known to have high rates of missing or misclassification of socially assigned race. Although this is concerning, 1) evidence indicates that EHR-based clinical data provides more objective estimates than claims-based data for sepsis surveillance [4], 2) any bias is likely toward the null (as most errors are of identifying LatinX patients as NHW) [103–105] and 3) there is no alternative. Further, we anticipate that some sites may use this project as an opportunity to highlight and correct for historical underinvestment in systematic, reliable capture of socially assigned race and other important demographics in their EHR. Third, Coalition turnover is expected to occur, limiting paired analyses of quantitative data. However, our prior research found that neither coalition size nor turnover was associated with intervention outcomes [30] (an association that we will evaluate in the proposed study as well). Further, organizations that were more successful in driving changes in organizational culture were observed to proactively adjust their coalition membership to adapt to changes in organizational leadership, to engage emerging champions, and to account for the specific aspects of AMI care they were addressing. Additionally, our study is designed to measure systems-level (rather than individual-level) phenomena, and we anticipate that the roles represented on the coalitions will remain relatively stable even as individuals come and go. Fourth, as with all health interventions there is a lag in time between implementation of practice change and corresponding adjustments in outcome rates. Subsequently, we plan to track difference in AA/B and NHW patients and LatinX and NHW patients for each of our clinical outcomes for 2.5 years post intervention implementing different lag periods (up to 6 months of lag time between the end of the intervention and time of observed clinical outcomes). Fifth, we may face limitations in attributing observed changes to the intervention. Hospitals will be exposed to multiple sources of knowledge during the intervention and may also undergo substantial internal shifts in staff and priorities. The mixed methods design of the proposed study is expected to allow us to capture and understand factors beyond the intervention that may be influencing the results.

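### The only sepsis case rule uses ICD-9-CM codes, which on an assumed October 2015 US switch to ICD-10-CM were assigned in none of the 20 study quarters

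*Protocol article*

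**What the plan says.** The Aim 3 section of the protocol article, under Sepsis Case Identification, says that sepsis admissions will be found "using validated International Classification of Diseases, Ninth Revision, Clinical Modification (ICD-9-CM) diagnosis procedure codes for infection and organ failure". It names the strategy and prefers it because it "is more sensitive than methods that use only ICD-9-CM codes for sepsis". No other case definition is given. The rule therefore selects the patients for time to antibiotic, in-hospital mortality and 30-day readmission alike.

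The calendar frame comes from three other places:

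- The abstract's Methods place the study in the United States: "deliver a coalition-based leadership intervention in eight U.S. health systems and their surrounding communities".
- Analytic approach sets the series: "We will consider a pre-exposure to the intervention time beginning 2.5 years (10 quarters) prior to starting the intervention". The follow-up side is equally long, at 10 quarters counted from the start.
- The Discussion shows that delivery still lay ahead during the pandemic: "the proposed study may be especially audacious in the context of COVID-19, which will likely strain organizational capacity to participate in change initiatives".

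No calendar start date is given. In its second limitation, the Discussion defends the use of EHR-derived outcome data partly on the ground that "EHR-based clinical data provides more objective estimates than claims-based data for sepsis surveillance".

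**The concern.** A case definition has to run on the data that exist in the study window. The article names one code set, and the window appears to lie wholly after US hospitals stopped assigning it. If so, the query returns nothing from native discharge codes, and whoever runs it must substitute another list that the article does not define.

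The case list fixes the denominators of the mortality and readmission gaps and the sample for time to antibiotic. The article also relies on the strategy being validated and comparatively sensitive. Both properties are claimed for the ICD-9-CM form. They may or may not hold for a translation, and nothing in the article lets a reader judge.

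There is a second, smaller point. The Discussion appeals to an advantage of EHR clinical data for sepsis surveillance, but a rule built on diagnosis codes does not use that advantage.

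**Working it through.** **1. The plan's own figure.** The only number tied to case identification is the expectation of at least 140 AA/B sepsis patients per system per year. Its inputs, all in the Aim 3 section, are an average inpatient volume of over 19,000, 12% AA/B and sepsis in 6% of adult hospitalizations:

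19,000 × 0.12 × 0.06 = 136.8 per year, or 136.8 / 4 = 34.2 per quarter.

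This is within 3% of 140. Exactly 140 needs 140 / (0.12 × 0.06) ≈ 19,444 admissions, which fits a volume of over 19,000. The projection is not an arithmetic error. It does depend on a 6% prevalence that the article does not tie to any particular code list. If a translated list captured 3% to 10% of admissions (illustrative values), the count would run from 19,000 × 0.12 × 0.03 ≈ 68 to 19,000 × 0.12 × 0.10 = 228.

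**2. Calendar count.** Let S be the first intervention quarter and C the first quarter coded in ICD-10-CM. The first quarter of the series is S − 10. The number of ICD-9-CM quarters is max(0, C − (S − 10)), up to a maximum of 20. It is zero whenever S ≥ C + 10.

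*Assumption, not in the article:* the US switch took effect on 1 October 2015, so C = 2015Q4 and C + 10 = 2018Q2.

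| Start quarter S (assumed) | First quarter of series | Last of the 20 quarters | ICD-9-CM quarters |
|---|---|---|---|
| 2018Q1 | 2015Q3 | 2020Q2 | 1 |
| 2018Q2 | 2015Q4 | 2020Q3 | 0 |
| 2020Q1 | 2017Q3 | 2022Q2 | 0 |
| 2021Q1 | 2018Q3 | 2023Q2 | 0 |
| 2022Q1 | 2019Q3 | 2024Q2 | 0 |
| 2023Q1 | 2020Q3 | 2025Q2 | 0 |

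**3. Sensitivity to the assumed switch date.** With the earliest COVID-era start tested, 2020Q1, the series opens in 2017Q3. That is seven quarters after 2015Q4, so the switch could have come up to seven quarters later and the count would still be 0 of 20. The lag of up to six months considered in the Discussion only extends follow-up later and adds no earlier quarter.

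**4. The code rule beside the EHR argument.** The Aim 3 section chooses diagnosis codes for sensitivity. The Discussion favours EHR clinical data over claims for objectivity. Both cite the same reference (number 4), which is also the source of the 6% prevalence. The two statements concern different properties, and the article does not say how they fit together.

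**The case against.** The strongest objection is that the main step needs a date from outside the article, while the article gives no start date. That is correct, and it is why the date is stated as an assumption and varied. The conclusion does not turn on the exact day: the pandemic reference and the 10-quarter lead-in leave a margin of seven quarters at the earliest COVID-era start tested.

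It can also be said that a journal article condenses, and that a code list may sit in the full protocol. That would excuse silence. Here the article is not silent: it names a code set and rests claims of validity and sensitivity on it. If a current list already exists, the repair is only a correction of wording.

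Three stronger readings are tempting and are not supported:

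- **The code rule contradicts the Discussion.** The Discussion compares EHR clinical data with claims, diagnosis codes held in an EHR are not claims data, and the Aim 3 section gives sensitivity as a separate reason. The statements are unreconciled, not contradictory.
- **Each site will translate the codes in its own way.** The Aim 3 section assigns case identification to the study team, and nothing delegates it to sites.
- **Coding drift during the programme could by itself produce a meaningful mortality effect.** The article gives no figures from which to size this. A shift in overall mortality is also the wrong comparator, because the 1% threshold concerns the difference between racial groups. Suppose extra cases make up 10% to 20% and carry half the fatality, equally in each group (invented inputs). Each rate, and so the gap, is multiplied by 1.05/1.10 = 0.955 to 1.10/1.20 = 0.917, a shrinkage of 4.5% to 8.3% of the gap. Drift common to changers and non-changers would also tend to cancel in the planned comparison.

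**Conclusion.** The point holds for the code set. As written, the case rule for all three Aim 3 outcomes finds cases in 0 of 20 quarters for any start from 2018Q2 onward. This rests on two assumptions: a US switch to ICD-10-CM on 1 October 2015, and a start during the COVID-19 period, as the Discussion implies. It is a rule stated wrongly, not a detail left for later. The stated validation and sensitivity cannot be presumed for whatever list replaces it.

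The link to the Discussion's EHR argument is a lesser matter of reconciliation. No size of bias in the racial gaps can be derived from the article, and none is claimed. The projected 140 cases per system per year stands as arithmetic.

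**What to change.** Replace the ICD-9-CM rule with one fixed ICD-10-CM list of infection and organ-failure codes. State that the study team applies it identically to all eight systems and all 20 quarters, and say what validation supports that list.

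Add a sentence reconciling the code-based rule with the Discussion's argument for EHR clinical data. An EHR clinical definition could be added as a sensitivity analysis. It need not be primary, and one that required antibiotic treatment would make case status depend on antibiotic receipt in a study where time to antibiotic is an outcome.

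The cost is small: revised wording and one centrally run code list, with no new data source, since outcomes already come from the EHR. The optional sensitivity analysis would add work to harmonise organ-dysfunction data across eight independent systems.

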
#### Analytic approach

We will conduct a comparative interrupted times series (ITS) analysis to examine the relation between the intervention and racial/ethnic differences in sepsis clinical outcomes between AA/B and NHW patients and between LatinX and NHWs. The analysis will be performed separately for our three key outcomes: 1) time to antibiotics, 2) in-hospital mortality, and 30-day readmission and stratified by response to the intervention (change/no change) (Additional File 1; Supplemental Fig. 5). We will consider a pre-exposure to the intervention time beginning 2.5 years (10 quarters) prior to starting the intervention and a postexposure period comprising 2.5 years (10 quarters) following the start of the intervention, with estimates made at every calendar quarter. ITS will be utilized to determine the difference in quarterly rates over time between changers (systems that responded to the intervention) and non-changers, health systems that did not respond to the intervention. Subsequently, ITS allows us to detect if an intervention has impact above and beyond secular trends when randomization is not a feasible option, and is ideal for evaluation of data collected across multiple equally spread time points by testing the changes in the slope of an outcome over time [96]. Additionally, ITS requires at least eight observations pre and post intervention [97]. We will utilize generalized mixed effect models in conjunction with segmented regression to evaluate the effectiveness of our intervention [98]. The model will control for patient-level characteristics, including age, sex, insurance status, Charlson Comorbidity index, and admission through the Emergency Department or transfer from another acute care facility, and hospital-level characteristics including size, academic vs community hospital, number of intensive care beds, annual sepsis case volume. We will also account for seasonality based on calendar quarter by including a “season” term alone and interacted with the treatment indicator and will assess for any residual autocorrelation using autoregressive integrated moving average (ARIMA). To allow a marginal interpretation of results, we will use a linear probability model for all analyses. Because outcomes of patients within a hospital are expected to be correlated, we will account for these non-standard variance–covariance structures by clustering at the hospital level. All coefficients will be modeled as fixed effects.

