Therefore, we aim to adapt, deliver, and evaluate a 2.5-year, coalition-based leadership intervention in eight U.S. health systems and their communities to improve the domains of organizational culture that are required to mitigate structural racism in sepsis care. We will adapt a proven intervention [27] that will develop and support Guiding Coalitions as they work to mitigate structural racism as a driver of racial inequities in sepsis care in their local context. We hypothesize that the intervention will generate longitudinal improvement in the domains of organizational culture that are required to mitigate structural racism in sepsis care. Using a longitudinal, convergent mixed methods approach we will: 1) quantify change in domains of organizational culture using a novel survey adapted from our previously validated instrument [28] (an innovation in measurement of structural racism), and 2) describe the experience of change within each system, integrating quantitative and qualitative data to develop a comprehensive understanding of impact and the mechanisms by which impact may have occurred. We also hypothesize that hospitals that demonstrate improvements in organizational culture will also demonstrate greater reductions in racial inequities in three sepsis-related outcomes: a) early identification (time to antibiotic), b) in-hospital mortality, and c) 30-day, all-cause hospital readmission, using comparative interrupted times series (ITS) analysis. The purpose of this paper is to present the theoretical foundation for the study, summarize key elements of the intervention, and describe in detail the study methodology to evaluate the intervention.

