## Methods/design

We will employ a robust, longitudinal mixed methods interventional study design that includes three aims: delivery of the intervention, evaluation of the impact of the intervention on organizational culture, and evaluation of the impact of the intervention on racial inequities in care and outcomes for patients with sepsis (Additional File 1: Supplemental Fig. 1). The study is projected to take place over a 5-year project period (Fig. 2). This description of the intervention and the associated evaluation has been prepared in alignment with the StaRI standards for the reporting of implementation studies (Additional File 2) [53].

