### Site selection and intervention (Aim 1)

*Overview:* We will adapt and deliver a coalition-based leadership intervention in eight U.S. health systems and their surrounding communities to improve domains of organizational culture that are required to mitigate structural racism, with reducing racial inequities in sepsis care and outcomes as a shared goal. We will support these eight health systems to establish Guiding Coalitions made up of administrative and clinical leadership involved in sepsis care, patient advocacy representatives, and community organizations poised to address the impact of structural racism through collaboration. We will engage these coalitions in a 2.5 year, facilitated leadership intervention grounded in double-loop learning [27, 54, 55] to apply a strategic problem-solving method [52] to measure, understand, and address structural racism as a driver of racial inequities in sepsis care in their local context.

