#### Intervention components

Based on our prior success in similar organizational change efforts [29], the 2.5 year intervention will include three components: 1) a series of five semiannual virtual, cross-site forums attended by four key members of each Guiding Coalition; 2) a series of four one-day workshops onsite with the full coalition at each hospital; and 3) a web-based platform to allow sites to share experiences and to serve as a repository for program resources. The content will build on and extend the previously published LSL curriculum [29]. *Semiannual forums* will bring sites together as a learning community for advice and problem solving on culture change to address structural racism in sepsis care. The sequence of forums will move sites from understanding and ‘buying in’ to the evidence base to sharing implementation challenges and successes. In the annual and closing forums, sites will vote for the “STAR” (Striving to Achieve the Remarkable) site that best exemplifies commitment to the objectives of the learning community, a highly motivational activity in LSL. *On site workshops* will build leadership capacity within the full Guiding Coalition to mitigate structural racism as it manifests in sepsis care. Each of the four workshops will include one full day of content, scheduled based on site preferences. The core curriculum for the workshops will incude both *how to work* (improving the domains of organizational culture that are required to mitigate structural racism and the underlying ecological barriers to health equity) and *what to work on* (strategic problem solving [52] to address root causes of inequities in sepsis care and outcomes in their site, see Additional File 1; Supplemental Fig. 2 for examples). In the first workshop, we will orient Guiding Coalition members to the intervention and the evidence base, promote reflection on their own measures of inequities in sepsis care and baseline organizational culture (survey measure described below), and name a problem statement and objective on which the group will focus their root cause analysis process. We will also invest in effective working relationships and processes among coalition members, including representation and role clarity [58], decision-making [59], and accountability [60]. Between workshops, the coalitions will be tasked with making and measuring progress toward addressing identified priority root causes of racial inequities in sepsis care in their home systems. At subsequent workshops, members will report on their progress, with the goal of solving implementation challenges and further developing their individual and group capacity for adaptive leadership [25, 26]. Additional workshop content will include diagnosing and shaping organizational culture, engaging conflict productively [61], using levels of analysis to diagnose organizational challenges [62, 63], and working with power and hierarchy [64, 65]. Content will be tailored to the local context by adjusting the timing of these modules to meet teams’ most pressing needs, adapting the specific examples and experiential learning exercises used in each module, articulating linkages between these content areas and ongoing work in each site, and encouraging each site to focus on root causes of inequities in sepsis care and treatment that are most salient in their environment. The facilitation team will include expert facilitators from across the United States, with backgrounds in organizational development, leadership education, anti-racist organizational change, and clinical quality improvement; most facilitators will be drawn from a faculty pool with deep experience developed through prior successful projects. Facilitators will work in teams of two or three, including a lead facilitator and additional experts tailored to the needs of each site. To promote standardization across sites while allowing for adaptation to local context, facilitators will use a fidelity checklist for each workshop. At the end of each workshop, the lead facilitator will prepare a structured written summary of decisions and action items for report back to the Guiding Coalition and to the full facilitation team. Between workshops, *a web-based information sharing platform* will serve two primary functions: (1) to serve as an accessible, up-to-date repository of project materials and references and (2) to support direct communication across hospital teams for sharing of successes, barriers, and project updates.

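### The outcome series stops when the 2.5-year intervention ends, but the promised lag analysis counts from that end, so it has no quarters of data

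*Protocol article*

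**What the plan says.** Three sections of the protocol article give the same duration. The Background sets out to "evaluate a 2.5-year, coalition-based leadership intervention in eight U.S. health systems", the Aim 1 overview says "We will engage these coalitions in a 2.5 year, facilitated leadership intervention", and Intervention components says "the 2.5 year intervention will include three components".

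The Analytic approach under Aim 3 then fixes the ITS window. The baseline is "a pre-exposure to the intervention time beginning 2.5 years (10 quarters) prior to starting the intervention", and the follow-up is "a postexposure period comprising 2.5 years (10 quarters) following the start of the intervention", with one estimate per calendar quarter. The same section says that the method needs at least eight observations on each side.

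The Discussion, in its fourth limitation, accepts that outcome rates respond to practice change only after a delay. Its answer is to follow the racial differences "for each of our clinical outcomes for 2.5 years post intervention implementing different lag periods", with "up to 6 months of lag time between the end of the intervention and time of observed clinical outcomes".

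Methods/design adds the outer limit: "The study is projected to take place over a 5-year project period".

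**The concern.** The two sections count from different points. The analysis counts its post period from the start of delivery; the limitation counts its lag from the end of delivery. Because the post period and the intervention are equally long, the defined series contains no quarter in which a lag counted from the end could be observed.

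This matters because the lag analysis is the article's stated remedy for a weakness that it acknowledges. If the analytic definition is followed, the remedy has no data. If the limitation is followed, the window in the methods is wrong. Left open, the choice of window and lag could be made after outcomes have been seen, and the window is part of what the ITS estimates.

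**Working it through.** **Inputs, all from the protocol article**
- Intervention length: 2.5 years (Background; Aim 1 overview; Intervention components).
- Pre and post periods: 10 quarters each, the post period counted from the start (Analytic approach).
- Minimum series length: eight observations before and eight after (Analytic approach).
- Lag: up to 6 months = 2 quarters, counted from the end (Discussion, fourth limitation).
- Project length: 5 years = 20 quarters (Methods/design).

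**Step 1. Reproduce the stated figure.** 2.5 years x 4 = 10 quarters. This agrees with the article. The intervention also lasts 2.5 x 4 = 10 quarters.

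**Step 2. Quarters after the end of delivery under the Analytic approach.** Post period minus intervention length = 10 - 10 = 0. All 10 post-exposure quarters are delivery quarters.

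**Step 3. Data for a lag counted from the end.** Usable quarters = max(0, 10 - 10 - L), where L is the lag in quarters. For L = 0, 1 and 2 the result is 0. Observing outcomes six months after the end needs data to quarter 10 + 2 = 12, which is 12 / 4 = 3.0 years after the start. The defined series falls 12 - 10 = 2 quarters short.

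**Step 4. The limitation read literally.** Tracking for 2.5 years after the end covers quarters 11 to 20 after the start. That gives 10 quarters after the end, or 10 - 2 = 8 after a two-quarter lag. The last quarter falls at 20 / 4 = 5.0 years after the start. The project is 20 quarters long, so 20 - 20 = 0 quarters remain for start-up or analysis.

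**Step 5. The lag counted from the start instead.** 10 - 2 = 8 post quarters, exactly the stated minimum. The article does not say this, but the plan would be internally consistent if it did.

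**Step 6. Can the ITS still be fitted?** Yes: 10 post-start quarters are at least eight. To see whether a gradual effect would be missed, assume that it builds linearly over delivery after a delay of d quarters: y(t) = -max(0, t - d) / 10 for t = 1 to 10, on a flat baseline. This shape is my assumption; the article gives none. The segmented least-squares slope change is the sum of (t - 5.5) y(t), divided by 82.5.
- d = 0: -8.25 / 82.5 = -0.100 per quarter, the full true slope.
- d = 2: -7.8 / 82.5 = -0.095 per quarter, 95% of it.

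The slope term therefore largely survives a six-month delay under this shape.

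**The case against.** The best defence is that the limitation is loosely worded. Its 2.5 years equals the length of the post period in the Analytic approach, so the phrase may simply mean the period after the intervention began. That reading is reasonable, and it removes both the conflict over window length and the clash with the 5-year project. It does not remove the conflict over the lag, whose origin is stated outright as the end of the intervention.

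A second defence is that this is a condensed article and that the study timeline figure and the supplemental ITS figure are not visible. They may show the intended window. They would not change the two statements, which are both in the text and disagree; this is not detail left for another document.

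A third is that starting the post segment at launch is legitimate, since coalitions are expected to act between workshops. This stands. A model with a slope-change term does not assume full exposure from the first day.

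A reader might go further and infer three things that the article does not support:
- **That the ITS has no post period and is void.** It has 10 quarters after the start and meets its own minimum.
- **That the effect will be heavily diluted, or the level term will take the wrong sign.** The plan proposes no simple before-and-after mean contrast, and its stated emphasis is on change in slope. Such figures would depend on an assumed effect shape and, for the level term, on how post-period time is coded. Delays beyond six months are not in the article.
- **That all outcomes precede the culture change meant to explain them.** The survey runs at launch, midpoint and end, and qualitative data come in waves. A change confirmed at the end need not have occurred at the end.

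**Conclusion.** The point stands as a conflict over the window and the lag origin. Following the Analytic approach as written leaves 0 quarters for any lag counted from the end of the intervention, and a six-month lag falls two quarters beyond the series. The result is calendar arithmetic on the article's own figures. It assumes only that delivery runs the full 2.5 years stated and that the post period opens when delivery opens.

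The conflict over total tracking time is weaker, because it depends on reading the limitation literally. The main ITS remains estimable. What cannot be done as described is the lag analysis offered as protection against delayed effects.

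**What to change.** State one time origin, one post-period length and one lag origin, in the same terms in the Analytic approach and the fourth limitation, before outcomes are analysed. Either of two routes works.

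1. **Keep the lag counted from the end and extend the series.** Add at least two quarters beyond the end of delivery: 10 + 10 + 2 = 22 quarters in total, ending 3.0 years after the start. That leaves 5.0 - 3.0 = 2.0 years of the project for start-up and analysis, assuming that the baseline quarters are extracted retrospectively. Two quarters is the floor: it lets outcomes be seen up to six months after the end. If the lag is meant as a gap to be skipped, the first usable quarter is 10 + 2 + 1 = 13 and a longer extension is needed. The cost is two or more further quarters of record extract from each system.

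2. **Keep the 20-quarter series and count the lag from the start.** This needs no further data, but a two-quarter lag leaves eight post quarters, with no margin over the stated minimum, and nothing is learned about outcomes after delivery ends.

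Under either route, reword the 2.5-year tracking statement in the limitation to match. Modelling delivery as its own segment is optional and not needed to resolve the conflict.
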